##### Process evaluation

The process evaluation will include concurrent fidelity assessment and a qualitative study (focus group/in-depth interviews) among students/teachers during the final stages of the trial to explore the implementation of the intervention and identify contextual factors associated with outcomes. Teachers will be provided with questionnaires to evaluate the Curriculum Guide and to provide feedback on their experience.

#### Plan of analysis

The study tools/measures will be examined for internal consistency. Demographic and baseline characteristics will be summarised using descriptive statistics. Principal-analyses will be intention-to-treat which will take into account clustering by the school and repeated measures. To assess the effectiveness of interventions, outcomes will be compared between two trial arms using linear-mixed-model analysis for continuous outcomes and generalised linear mixed models or generalised estimating evaluation (GEE) for binary outcomes. The analysis will include all participants with at least one outcome measurement at 6 weeks post-intervention. A per-protocol analysis will also be conducted along with intention-to-treat analysis to examine the influence of missing data patterns. Multiple imputation will be attempted for missing values. The analysis will be adjusted for potential confounders that are identified a-priori during the study. Subgroup analysis will be performed for important socio-demographic variables. Statistical significance will be set at *p*-value< 0.05, and Bonferroni’s correction will be made for multiple testing (if any).

For qualitative analysis, all the verbatims of interviews/group discussions will be transcribed and translated into English for thematic analysis.

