### Exclusion criteria

(1) Children who did not give informed assent (2) Children whose parents/guardians did not provide written informed consent (3) Children who were absent for the baseline assessment even after two attempted visits (4) children aged> 15 years at enrolment.

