##### Timing of outcome-measurement

Data will be collected using self-administered questionnaire. Students will complete the survey during class time in the presence of trained project assistant/ teacher to assist the children with reading, writing and answering any queries. Data will be collected at 4-timepoints from both intervention and control schools: baseline and 6-weeks, 6-months and 12-months post-intervention (Fig. 2). To maximise data completeness, all effort will be made to obtain data from absentee students through liaison with key school-staff.

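### The rule limiting the analysis to pupils measured at 6 weeks conflicts with the stated intention-to-treat, repeated-measures analysis and, as written, drops pupils who have later data

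*Protocol article*

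**What the plan says.** The statements that matter are in the protocol article.

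- Principle (Plan of analysis): "Principal-analyses will be intention-to-treat which will take into account clustering by the school and repeated measures".
- Model (same section): "outcomes will be compared between two trial arms using linear-mixed-model analysis for continuous outcomes".
- Analysis set (same section): "The analysis will include all participants with at least one outcome measurement at 6 weeks post-intervention".
- Missing data (same section): "Multiple imputation will be attempted for missing values", and "A per-protocol analysis will also be conducted along with intention-to-treat analysis to examine the influence of missing data patterns".
- Visits, in both arms (Timing of outcome-measurement): "baseline and 6-weeks, 6-months and 12-months post-intervention". For absent pupils the same section promises that "all effort will be made to obtain data from absentee students through liaison with key school-staff".
- Enrolment (Exclusion criteria): the excluded include "Children who were absent for the baseline assessment even after two attempted visits". Every enrolled pupil should therefore have a baseline assessment.

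**The concern.** Whether a pupil has a 6-week measurement is settled after schools are allocated and after the intervention is delivered. A population chosen on that event is a modified, available-case set, not the intention-to-treat set named in the same paragraph. The restriction is also unnecessary, because a repeated-measures mixed model can use a pupil's 6- and 12-month scores when the 6-week score is absent.

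The main stake is selection. The Blinding section describes an open-label trial, and the Objectives and Exploratory outcomes list absenteeism among the things the intervention may influence. If presence at 6 weeks depends on arm and is related to the outcome, conditioning on it distorts the comparison at every visit, including the 12-month one. The lesser stake is the discarded later data.

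**Working it through.** **1. Reading the rule against the rest of the plan.** Take a pupil with baseline, 6-month and 12-month scores and no 6-week score.

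- Under the intention-to-treat, repeated-measures statement, the pupil is analysed in the allocated arm.
- Under the analysis-set sentence, the pupil is excluded. Taking the wording to mean any one of the scales at 6 weeks changes nothing for a pupil absent from that survey.
- The Interim-analyses section has its own 6-week analysis, but the analysis-set sentence is not confined to it.
- Imputation can fill later visits or missing scales for included pupils. It cannot serve a pupil already removed.
- The per-protocol set is not defined. Whether it means adherent pupils or completers, it does not bring the pupil back or vary the assumption about missing scores.

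**2. Reproducing the plan's power figures.** Inputs from Sample size and power: 4 schools per arm, m = 50 pupils per school, ICC 0.01 to 0.05, two-sided 5%, 85% power.

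Design effect DE = 1 + (m − 1) × ICC; standard error SE = √(2 × DE / (4m)) in SD units; detectable difference = (1.960 + 1.036) × SE.

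- ICC 0.01: DE = 1 + 49 × 0.01 = 1.49; SE = √(2 × 1.49 / 200) = 0.122; detectable difference 0.366 (stated 0.37).
- ICC 0.05: DE = 1 + 49 × 0.05 = 3.45; SE = √(2 × 3.45 / 200) = 0.186; detectable difference 0.557 (stated 0.56).

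Power at the stated differences is 85.8% and 85.4%. With 5% loss (m = 47.5) it is 84.6% and 84.9%, which agrees with the plan's claim of more than 80%.

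**3. Power if the 6-week rule shrinks the set.** The absence rates, and the assumption that 50–80% of absentees return later, are mine. Power = Φ(d / SE − 1.960), with m reduced accordingly.

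| Absent at 6 weeks | Pupils dropped of 400 | Of these, measured later | Power, ICC 0.01, d = 0.37 | Power, ICC 0.05, d = 0.56 |
|---|---|---|---|---|
| 5% | 20 | 10–16 | 84.6% | 84.9% |
| 10% | 40 | 20–32 | 83.3% | 84.4% |
| 20% | 80 | 40–64 | 80.2% | 83.1% |

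Example: at 10% and ICC 0.01, m = 45, DE = 1.44, SE = √(2 × 1.44 / 180) = 0.1265, and 0.37 / 0.1265 − 1.960 = 0.965, giving 83.3%. The comparison is with complete data, so it is an upper bound on what the fix recovers.

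**4. Bias, on assumed inputs.** If absentees score 0.5 SD below those present, the retained mean in an arm is raised by 0.5 × (absence rate). With 5% and 15% absence the arm difference shifts by 0.5 × (0.15 − 0.05) = 0.05 SD, which is 0.05 / 0.56 = 9% to 0.05 / 0.37 = 14% of the target difference.

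A simulation with no true effect, in which absence depends on the pupil's own outcome equally strongly in both arms, gave:

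| Absence, arm A / arm B | Log-odds of absence per SD lower score | Shift (SD) |
|---|---|---|
| 5% / 5% | 0.5 | −0.001 |
| 10% / 10% | 0.5 | −0.002 |
| 5% / 15% | 0.5 | 0.048 |
| 10% / 20% | 0.5 | 0.047 |
| 5% / 15% | 1.0 | 0.086 |

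Against the standard errors in step 2, 0.05 SD is 0.05 / 0.186 = 0.27 to 0.05 / 0.122 = 0.41 of one SE, and 0.086 SD is 0.46 to 0.70.

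**The case against.** The wording may be a slip. Asking for at least one measurement at a single visit is odd, and the authors may have meant any measurement from 6 weeks onward, which would suit the repeated-measures model. That is plausible, but no section says it, and on that reading the sentence still has to be corrected.

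The harm is also conditional. The plan commits to pursuing absentees, gives no reason to expect unequal absence, and keeps more than 80% power at 10% or even 20% absence. All of that stands, and it limits the size of the point.

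A reader might infer three stronger things that the article does not support:

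- *That the rule contradicts the planned multiple imputation.* The conflict is partial: imputation keeps a role for included pupils.
- *That the per-protocol set selects on adherence and so adds a second selection.* The article does not define the set, and its stated purpose would also fit a completers set. What can be said is that neither version checks the missing-data assumption.
- *That the result will be biased by about 0.05 SD.* That is one assumed scenario, and with equal absence the shift is about zero.

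The proposed set is not free of post-allocation selection either. The order of steps in Randomisation, Student-recruitment and Intervention-schools appears to put consent and baseline after school allocation. Baseline does precede delivery of the intervention, so the selection is narrower, but the fix does not remove it.

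**Conclusion.** The point holds as a conflict between two statements in one paragraph: the stated principle is intention-to-treat with repeated measures, and the stated population is not. Followed literally, the rule drops allocated pupils who have usable later data, and neither named safeguard puts them back.

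Selection matters more than power here. Bias runs from about zero, with equal absence and the same link to outcome in both arms, to about 0.05–0.09 SD with 5% against 15% outcome-related absence. Those inputs are assumptions. Power is about 83–84% at 10% absence against the stated 85%. The documents do not show that bias will occur, and the mixed model on the wider set removes it only as far as observed scores explain the absence.

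**What to change.** Replace the analysis-set sentence with:

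> All enrolled pupils (consented, with a baseline assessment) are analysed in the arm to which their school was allocated; the mixed model uses every available post-baseline measurement at 6 weeks, 6 months or 12 months, whether or not the 6-week one is present.

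State that pupils with no post-baseline measurement are handled by the planned multiple imputation or by modelling baseline as an outcome; without one of these they would contribute nothing. A set restricted to 6-week data can be kept for the interim analysis or as a sensitivity analysis.

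Stop describing the per-protocol analysis as the check on missing data. A sensitivity analysis that shifts imputed scores is an optional addition for the statistical analysis plan, and its absence from the article is not a fault.

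The cost is a few sentences and no extra data collection. The article places recruitment in the future, and the change is best made before the 6-week interim data are seen, since redefining the population afterwards would be open to challenge.

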#### Primary outcome

The primary outcome, **Positive mental health literacy** will be measured using a 10-item Mental Health-Promoting Knowledge (MHPK-10) scale. It is a valid and reliable one-dimensional instrument measuring knowledge of factors promoting good mental health among adolescents. The MHPK-10 had demonstrated good internal validity and test-retest reliability (r = 0.74) among adolescents. For each item, respondents rate items on 1–5 likert-type scale, the extent to which they are correct or wrong. The score range is 10–50, with a higher score indicating a higher positive mental health literacy [26].

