##### Sample size and power

Positive mental health literacy measured using the 10-item Mental Health-Promoting Knowledge (MHPK-10) scale is considered primary outcome for the present study [26]. However, the Intra-Cluster Correlation for MHPK-10 score is unknown. Based on evidence from similar adolescents studies, we assumed a conservative and modest estimate of ICC (ρ) between 0.01 and 0.05 [34, 35]. From the Kolar District Report (as on 30/3/2016), an estimated average of 50 students is expected from grade-6 and 7 of each higher-primary schools. With a need for 4 schools per arm with 50 students per school, we powered the trial to be able to detect a standardised difference (difference in means/SD) of 0.37–0.56 (medium effect size) for MHPK-10 scores between intervention and control groups for a two-sided level of significance at 5% (*α* = 0.05) with 85% power. For the above assumption, the design effect varied from 1.5 to 3.5 for ICC (ρ) values from 0.01 to 0.05, respectively [36]. We expect a minimum sample size of 400 across 8 schools for 85% power. Even with a 5% loss to follow-up, the study will still have more than 80% power.

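### The covariate rule contradicts itself, the baseline score has no stated role in the model, and no small-sample inference is named for a trial of 8 schools

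*Protocol article*

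**What the plan says.** The Plan of analysis (protocol article) gives an intention-to-treat analysis that allows for school clustering and repeated measures, "using linear-mixed-model analysis for continuous outcomes and generalised linear mixed models or generalised estimating evaluation (GEE) for binary outcomes". On covariates it says only: "The analysis will be adjusted for potential confounders that are identified a-priori during the study". It lists none.

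Baseline is one of the four data collection points (Timing of outcome-measurement). Pupils who miss the baseline assessment after two attempted visits are excluded (Exclusion criteria). The primary scale is reported to have "test-retest reliability (r = 0.74) among adolescents".

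Sample size and power rests on these statements: "With a need for 4 schools per arm with 50 students per school", "we assumed a conservative and modest estimate of ICC (ρ) between 0.01 and 0.05" and "We expect a minimum sample size of 400 across 8 schools for 85% power". The Blinding section makes the trial open-label, with the statistician blinded until database lock.

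**The concern.** Three features of the same short section bear on the primary test.

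- **Covariates.** The sentence gives two incompatible times for choosing them. Read one way, the set is fixed beforehand. Read the other way, it can be settled after data have been seen. With 8 schools there are only 6 between-school degrees of freedom, so each school-level covariate is expensive.
- **Baseline score.** By design every enrolled pupil has one, and it is usually the most useful covariate available. The text does not say whether it is a covariate, one more repeated measure, or unused. These choices differ in precision.
- **Reference distribution.** Wald z tests and uncorrected sandwich errors rely on many clusters. The plan names no alternative, and the sample size itself was worked with normal quantiles.

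At stake are the true level of the nominal 5% test and precision that costs nothing to recover.

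**Working it through.** **Inputs.** From Sample size and power: 4 schools per arm, 50 pupils per school, two-sided 5%, 85% power, ICC 0.01 to 0.05, standardised difference 0.37 to 0.56. The article gives no baseline-to-follow-up correlation r, so I assume 0.3, 0.5 and 0.74. The last borrows the test-retest figure as an upper bound.

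**1. The plan's own figures.** Design effect = 1 + 49 × ICC = 1.49 and 3.45. SE = √(2 × DE / 200) = 0.122 and 0.186. Detectable difference = (1.960 + 1.036) × SE = 0.366 and 0.557. Normal-theory power at 0.37 and 0.56 is 85.8% and 85.4%. The stated figures are reproduced, with normal quantiles.

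**2. The same design on t.** Degrees of freedom = 2 × (4 − 1) = 6, with critical value 2.447. The noncentrality is 0.37/0.122 = 3.03 and 0.56/0.186 = 3.02. Noncentral t power is 71.5% and 71.1%.

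**3. Type I error at nominal 5%.** Simulated null trials (200,000 to 400,000 per ICC), 4 + 4 schools of 50, continuous outcome, one time point:

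| Test | ICC 0.01 | ICC 0.05 |
|---|---|---|
| REML mixed model, Wald z | 6.4–6.5% | 9.3% |
| Uncorrected sandwich, Wald z | about 14% | about 14% |
| School-level t, 6 df | 5.0% | 5.0% |
| REML mixed model, t on 6 df | 2.4% | 4.5% |

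Closed forms agree. Using 1.96 on 6 df gives 9.8%, the limit for REML with z. The uncorrected sandwich divides by 8 where 6 is needed, so its level is P(|t₆| > 1.96 × √(6/8)) = 14%. At ICC 0, REML with z gives 3.9%, so the inflation depends on the ICC.

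**4. Gain from the baseline score.** Suppose it explains pupil-level variance only. Variance of a school mean = ICC + (1 − ICC)(1 − r²)/50, and SE = √(2 × variance / 4). Power on 6 df at the stated differences:

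| r (assumed) | ICC 0.01, d = 0.37 | ICC 0.05, d = 0.56 |
|---|---|---|
| no baseline | 71.5% | 71.1% |
| 0.3 | 74.1% | 72.1% |
| 0.5 | 78.9% | 74.1% |
| 0.74 | 88.3% | 77.8% |

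Example for r = 0.5, ICC 0.01: 0.01 + 0.99 × 0.75/50 = 0.02485; SE = 0.1115; noncentrality 3.32; power 78.9%.

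If baseline also explained school-level variance in the same proportion, power would be about 75%, 82–83% and 96%.

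**5. Why the role of baseline matters.** For a change score, replace (1 − r²) with 2(1 − r), holding school variance equal. Power is then 61.6%/66.7% at r = 0.3, and at r = 0.5 it equals the unadjusted 71.5%/71.1%.

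**6. Cost of school-level covariates.** At d = 0.37 and ICC 0.01, with no gain in variance, power falls from 71.5% on 6 df to 68% on 5, 63% on 4 and 54% on 3.

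**The case against.** The strongest reply is that a degrees-of-freedom method, a sandwich correction and the exact model terms are ordinary content of a statistical analysis plan, which is not shown. That is fair, and it rules out several stronger readings that a reader might infer.

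- **That the baseline score is left out.** Not established. Baseline is one of the four time points and the model handles repeated measures, so it may already be in. If the arms' baseline means are constrained equal, that model recovers essentially the precision of covariate adjustment. The change-score loss in step 5 arises only if they are left free.
- **That the 5% test is inflated.** Not established. No z reference is prescribed; the figures apply only if one is used.
- **That 14% applies to the primary outcome.** It does not. GEE is named only for binary outcomes, and only as an alternative to a mixed model. The 14% also comes from a continuous-outcome simulation.
- **That the analysis model causes the fall to 71% power.** It comes from the normal quantiles in the sample size calculation. Correcting the test's level exposes that shortfall and does not cure it.
- **That covariates will be chosen post hoc.** The text also says they are set beforehand, and the statistician's blinding until database lock limits selection by arm. Nothing says that they would be several or school-level.

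What remains is that the covariate sentence is contradictory as written, which an unseen plan does not repair. In addition, the sample size shows that the small number of schools was not allowed for, so inference is more than a missing detail.

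**Conclusion.** The point holds in a limited form. The covariate rule contradicts itself and needs replacing. The role of baseline is unstated, and small-sample inference is neither named in the analysis nor allowed for in the sample size.

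For the primary outcome the exposure is a type I error of roughly 6.4% to 9.3%, conditional on a Wald z reference, ICC 0.01 to 0.05, equal school sizes and a single time point. The benefit of stating baseline adjustment is about 1 to 17 percentage points of power on 6 df under pupil-level adjustment: the smallest from 71.1% to 72.1%, the largest from 71.5% to 88.3%. It depends wholly on the assumed r. The 0.74 is a test-retest reliability, not a correlation with scores 6 weeks to 12 months after an intervention, so the top figure is a ceiling for this calculation. At ICC 0.05, pupil-level adjustment does not restore 85% power at any r considered.

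**What to change.** Replace the covariate sentence with a stated primary model along these lines:

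*The primary analysis is a linear mixed model for post-intervention MHPK-10 with arm, time, arm × time, baseline MHPK-10 and a short covariate list fixed before allocation, with random school and pupil effects and Kenward-Roger or between-within (6 df) inference.*

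- An equivalent repeated-measures model with baseline means constrained equal would serve as well.
- Keep the covariate list to pupil-level variables where possible, because each school-level term uses one of the 6 df.
- Use each secondary scale's own baseline in the same way.
- For binary outcomes, use a school-level analysis on 6 df, or GEE with a small-sample sandwich correction and t on 6 df.

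The cost is wording only: the baseline assessment is already planned and no extra data are needed. The downside is wider but valid intervals. At very low ICC the mixed model on 6 df is also somewhat conservative (2.4% at ICC 0.01 in step 3).

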### Outcomes

The following core outcomes will be used to assess the intervention. All outcome measures will be measured at the individual student level.

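### Holm's step-down procedure would serve better than the named single-step Bonferroni correction: a cheap improvement to a valid plan, not the repair of an error

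*Protocol article*

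**What the plan says.** The Plan of analysis sets one threshold and one correction: "Statistical significance will be set at *p*-value< 0.05", and "Bonferroni’s correction will be made for multiple testing (if any"). It does not say which tests form the family or how many there are.

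The Outcomes section opens with "The following core outcomes will be used to assess the intervention". It then names one primary outcome (MHPK-10) and, under Secondary outcomes, six scales: MHLS, PMHSS personal stigma, RIBS, IASMHS, K6 and CD-RISC. An interview schedule with case vignettes on first-aid knowledge and intentions follows under the same heading.

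Sample size and power concerns MHPK-10 alone. It targets a "standardised difference (difference in means/SD) of 0.37–0.56 (medium effect size) for MHPK-10 scores between intervention and control groups", with 85% power and an uncorrected two-sided 5% level. No power, effect size or correlation is given for any secondary scale.

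**The concern.** The multiplicity method is a stated choice, so this is not a detail left to an unseen analysis plan. Another procedure gives the same protection against false positives and never rejects fewer hypotheses.

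The secondary outcomes carry much of the trial's purpose. The Objectives cover knowledge, attitudes toward mental illness and first-aid behaviours, but the primary scale measures only knowledge. Attitudes and first aid rest on secondary measures, in a trial of eight schools. A real effect there that just misses the Bonferroni threshold would be reported as not significant, although Holm might have rejected it.

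**Working it through.** **1. The plan's own figure.** Inputs from Sample size and power: 4 schools of 50 students per arm (200 per arm), ICC 0.01 to 0.05, two-sided 5%, 85% power.

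- Design effect = 1 + (50 − 1) × ICC = 1.49 and 3.45. The plan says "the design effect varied from 1.5 to 3.5".
- Detectable difference = (1.960 + 1.036) × √(2 × design effect / 200) = 2.996 × √0.0149 = 0.366 and 2.996 × √0.0345 = 0.557. The plan gives 0.37 and 0.56.

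The figures reproduce with a normal reference and an uncorrected 5% for one outcome. Exchanging Bonferroni for Holm changes none of them.

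**2. The two procedures with m = 7.** Seven is an assumption: six scales plus the vignettes counted once.

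- Bonferroni tests every hypothesis at 0.05/7 = 0.0071.
- Holm orders the p-values and compares them in turn with 0.05/7, 0.05/6, …, 0.05/1 (0.0071, 0.0083, 0.0100, 0.0125, 0.0167, 0.0250, 0.0500), stopping at the first failure.

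The first step is the Bonferroni step, so the chance of at least one rejection is identical. Later thresholds are larger, so everything Bonferroni rejects is also rejected by Holm. When Holm first reaches a true null, its threshold is at most 0.05 divided by the number of true nulls. The family-wise error therefore stays at or below 5% with no assumption about dependence.

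**3. Bonferroni power per real effect.** Assume each real effect has 85% power uncorrected, that is, a mean test statistic of 1.960 + 1.036 = 2.996. The two-sided critical value at 0.0071 is 2.690. Power = Φ(2.996 − 2.690) = Φ(0.306) = 62%, however many effects are real.

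**4. Holm power, by simulation.** Seven equally correlated normal statistics, 100,000 to 200,000 runs per setting. The documents give no correlation, so 0, 0.3, 0.5 and 0.8 were tried.

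| Real effects of 7 | Bonferroni | Holm, correlation 0.3 to 0.5 | Holm, correlation 0 to 0.8 |
|---|---|---|---|
| 1 | 62% | 62% | 62% |
| 3 | 62% | 64–65% | 64–65% |
| 5 | 62% | 68% | 67–68% |
| 7 | 62% | 73–74% | 71–75% |

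- With all seven real and correlation 0.3, Holm finds about 5.2 effects on average and Bonferroni about 4.3.
- With all seven real and correlation 0.5, the chance of at least one rejection is 93.7% under both.
- The largest simulated family-wise error was 4.95% for both.

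**5. Other family sizes.** Six tests (threshold 0.0083) give Bonferroni 64%; eight (0.00625) give 60%. With all effects real and correlation 0.5, Holm gives 74% and 72%.

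**The case against.** Bonferroni is conventional, inflates no error rate and contradicts nothing else in the article. No power is promised for a secondary scale, so none that was promised is lost. This stands, and it is why the point is an improvement and not a correction.

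The family is not fixed either. The words on multiple testing could mean the three follow-up times, the subgroups, the exploratory outcomes or the secondary scales. This also stands: the seven-test family is an assumption, and so is every power figure built on it. The ranking of the methods does not depend on it, because Holm rejects at least as many hypotheses in any family.

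Bonferroni also has simple simultaneous confidence intervals that match its tests, and Holm does not. That is a real trade-off, but a small one here, because the article promises no such intervals.

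A reader might infer that correlation between the scales is what makes Bonferroni wasteful and Holm better. The calculation does not support that. Holm does not use correlation, and under the normal reference its gain with all seven effects real shrinks from about 13 points at correlation 0 to about 9 at 0.8.

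**Conclusion.** The point holds as an inexpensive gain in efficiency. Holm keeps the same 5% family-wise control and is never less powerful. The gain in average power per real effect runs from about 0 points (one real effect) through 2 to 3 (three) and 6 (five) to about 11 or 12 (all seven, correlation 0.3 to 0.5). It rests on three assumptions that the article does not supply: a family of seven, 85% uncorrected power for each real secondary effect, and a normal reference.

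Three stronger readings are tempting and unsupported:

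- That the plan is in error, or gives power away for nothing. Bonferroni is valid and has matching simultaneous intervals.
- That each secondary scale will be tested at 0.0071. The article never says so.
- That the trial's stated power suffers. That power belongs to MHPK-10 at an uncorrected 5%.

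**What to change.** In the Plan of analysis, replace the Bonferroni clause with wording such as: 'The secondary outcomes form one family and will be tested with Holm's step-down procedure at a two-sided family-wise 5%. Holm-adjusted p-values will be reported with 95% confidence intervals, which are not adjusted for multiplicity and are labelled as such.' List the members of the family in the same place.

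The cost is this text and one line of code; sample size and data collection are untouched. The article expects recruitment after March 2022, so as written the plan could be changed before any data are seen. The downside is that an unadjusted interval may exclude zero where the Holm-adjusted test is not significant, and the report should say so. If simultaneous intervals that match the tests matter more to the investigators than extra rejections, keeping Bonferroni is defensible.
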